### Patient and public involvement

Patient partners were involved in the design of the study and highlighted the relevance and need for this study. They will continue to be an integral part of the research team, offering advice from conducting the study through to interpretation of the data and dissemination of findings.

### Participant recruitment

Patients aged 18–60 that meet the Quebec Task Force Classification of WAD2 will be recruited within 4 weeks of injury. Participants will be recruited from emergency departments and minor injury units in Surrey, Sussex, Kent and Oxfordshire, directly by clinicians, and following weekly hospital database searches using defined search terms (eg, motor vehicle collision, muscle injury: neck, bruise/contusion/abrasion: neck, sprain/ligament injury: cervical spine). Potential participants will be contacted in person, or by phone, and asked for permission for their details to be passed on to the study team, and/or sent the study details. In addition, posters will be displayed in departments with study contact details. Healthy age-matched and gender-matched control participants will be recruited through departmental emailing lists (Universities of Sussex and Oxford as well as local hospitals), social media and flyers on public notice boards. Potential participants will be screened for suitability via telephone and also be invited to take part in the substudy. Eligible individuals will be sent a participant information sheet and questionnaires to complete (please see table 1 and questionnaire section below) and will be invited to attend a baseline appointment at either Brighton and Sussex Medical School, University of Sussex, Falmer or the Nuffield Department of Clinical Neurosciences, University of Oxford.

**Table 1 T1:** Summary of self-reported and physical assessments

Test	Description	Type of tool/assessment	Participants
Demographics	Age, gender, height/weight.	Self-reported.	HC and whiplash
Injury details	Impact, anticipation.	Self-reported.	Whiplash
Medication details	Specific to WAD symptoms.	Self-reported.	Whiplash
Symptom history	Description of pain or symptoms.	Self-reported.	Whiplash
Pain level	Current pain severity.	Visual Analogue Scale.	Whiplash
Management	Any investigations/treatment.	Self-reported.	Whiplash
Type of pain	Neuropathic pain.	painDETECT Questionnaire.	Whiplash
Disability	Neck disability.	Neck Disability Index.	Whiplash
Psychological factors	Post-traumatic stress. Pain catastrophising. Depression, anxiety and stress. Quality of life.	PTSD-8. Pain Catastrophising Scale. DASS 42. EQ-5D-5L.	Whiplash
Active range of motion	Cervical spine. Glenohumeral joints. Elbow, wrist and hands.	0–3 scale (0=full range, no symptoms; 1=full range, symptoms; 2=reduced range, no symptoms; 3=reduced range, symptoms).	HC and whiplash
Standardised neurological examination	Sensation (dermatomes C5–T1). Myotomes (C5–T1). Reflexes (biceps, triceps).	Cotton wool (light touch). Neurotip (pinprick). Isometric muscle contraction. Reflex hammer.	HC and whiplash
Bedside sensory testing	Sensation—main pain area and index finger (median nerve/C6 innervation).	Warm/cold coin (thermal) and Neurotip (pinprick).	HC and whiplash
Quantitative sensory testing—index finger	Warm/cold sensation/pain thresholds. Mechanical detection thresholds. Mechanical pain thresholds.	MSA thermal stimulator (Somedic, Stockholm, Sweden). Von Frey filaments (Marstock NerveTest filaments, MRC Systems, Heidelberg, Germany). Weighted pinprick stimulators (MRC Systems, Heidelberg, Germany). Vibration (Tuning fork). Pressure pain threshold (Algometer, Wagner Force dial, Greenwich, USA).	HC and whiplash
Heightened nerve mechanosensitivity	Upper limb neurodynamic test 1 (median nerve bias). Upper limb neurodynamic test 3 (ulnar nerve bias). Nerve palpation. Brachial plexus. Median nerve proximal to carpal tunnel. Ulnar nerve (Guyon’s canal). Ulnar nerve (proximal to cubital tunnel). Median nerve (carpal tunnel). Phalens. Tinels.	Positive/negative test (symptom response changes with structural differentiation). Inclinometer (ROM degrees). Positive/negative test (symptom response changes with structural differentiation). Digital palpation (0–3: 0=no pain or discomfort, 1=local discomfort, 2a=local painful response, 2b=referred pain/symptoms). Algometer and score (0–3). Digital palpation (0–1).	HC and whiplash
MRI	Brachial plexus. Wrist.	T2-weighted images. Diffusion tensor images.	HC and whiplash
Serum samples	Venepuncture.	Inflammatory markers.	HC and whiplash
Skin samples	Skin biopsy.	Density of dermal and intraepidermal nerve fibres using immunohistochemistry.	HC and whiplash

*EQ-5D-5L, Quality of life questionnaire

DASS, Depression, Anxiety and Stress Subscale; HC, healthy controls; PTSD, post-traumatic stress disorder; ROM, range of motion; WAD, whiplash-associated disorder.

Exclusion criteria include pregnancy, recent history of cervical/arm pain lasting >3 months, previous diagnosis of a peripheral neuropathy, history of systemic illness or autoimmune disease, non-medically controlled hypertension and ongoing steroid treatment. Participants will be assessed for their suitability to undergo MRI. Additionally, healthy control participants must not have had a history of whiplash injury and have not received treatment for neck, thoracic spine or upper limb pain within the past 3 months.

Both recruitment methods and experimental design, in particular length of time of research appointments and MRI scanning, have been discussed and modified based on the comments received from our patient advisory group.

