## Methods and analysis

### Objectives

The first objective of this study is to determine the presence of peripheral neuroinflammation during the acute stage following a WAD2 injury. This objective will use MRI to assess the extent of peripheral neuroinflammation and nerve microstructure in a cross-section of patients within 4 weeks of injury and healthy controls. The second objective will determine whether the presence of peripheral neuroinflammation in the acute stage can predict patient recovery status at 6 months. The third objective will determine the course of peripheral neuroinflammation from the acute to chronic stages of a WAD2 injury. For this objective, we will examine changes in MRI measures and clinical tests from baseline to 6 months in both recovered and non-recovered patients. The fourth objective will determine whether low-cost clinical tests can serve as markers to detect neuroinflammation as determined on MRI. The objective of the substudy is to determine whether the structural integrity of cutaneous nerve fibres is altered in the acute stage following a WAD2 injury, and whether it contributes to the progression to chronicity.

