### Study design

This is a prospective cohort study at two centres. A total of 115 participants will be recruited following a whiplash injury within 1 month of their original injury. We will also recruit 34 healthy proportionally age-matched and gender-matched control participants. People with acute WAD2 and healthy control participants will attend a baseline appointment. In addition to MRI, a detailed musculoskeletal assessment will be performed, as well as tests of nerve trunk mechanical sensitivity and quantitative sensory testing (QST). A blood sample will be taken and analysed for levels of inflammatory markers. Participants will also be asked to complete a series of validated questionnaires to assess neuropathic symptoms, functional deficits, quality of life and psychological factors. For the substudy, skin biopsies from the index finger and ankle will also be taken. At 6 months, the Neck Disability Index and a self-rated global recovery question will be used to determine recovery. A sequential sample of patients will be invited to attend a follow-up appointment during which the same detailed assessments will be repeated (figure 1).

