#### Follow-up

All participants will be asked to complete the questionnaires and answer a self-rated global recovery question 6 months after their injury. Twenty five participants who have recovered and 25 who have not recovered will undergo the full protocol. To promote participant retention, a newsletter will be sent to participants to keep them up to date about the study, and a small payment will be given to those who return their completed questionnaires at 6 months or attend their follow-up appointment.

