### Sample size calculation

Mean nerve signal intensity ratio data from our previous cross-sectional study of 13 controls and 9 participants with chronic WAD2 were analysed using a linear mixed model.^9^ The observed difference in means between controls and WAD2 participants was 0.0600 (SE=0.0315) for the C5–C8 roots of the brachial plexus, which was statistically significant; age was not a statistically significant covariate. The intraclass correlation coefficient of the nerve signal ratio was estimated to be 0.45. Assuming that there are eight assessments per participant (two sides × four roots), a SD of 0.1, intraclass correlation coefficient of 0.45 and a ratio of 3 participants with whiplash to one healthy control, the study would require 48 participants with whiplash and 16 controls to detect an effect estimate of 0.06 for the mean nerve signal intensity difference (80% power, 5% significance). Since in the acute stage it is estimated that only 50% of the participants with whiplash will develop chronicity,^51^ we will need to image 96 participants with whiplash and 32 controls for objective 1 (difference in neuroinflammation in the acute stage). Based on ~48 participants who have not recovered at 6 months, we would be able to fit a logistic regression model with 5–10 predictor variables for objective 2 (predictive factors of chronicity).

For objective 3 (development of neuroinflammation over time), we will ask 25 participants who have recovered and 25 participants who have not recovered to return at 6 months, which will enable an effect size of 0.9 to be detected using analysis of covariance, with 95% power for 5% significance. This value assumes that the correlation between the acute and chronic measurements is 0.5.

For objective 4 (validity of low cost tests of neuroinflammation), with nine independent variables, a rule of thumb for a multiple linear regression (ie, 10 participants per additional variable) implies that data from 90 participants with whiplash should be adequate to explore this.^52^

For the substudy, 68 participants with whiplash and 34 healthy controls (80% power, 5% significance, 0.53 effect size, one-tailed test) would allow the detection of a 20% smaller difference in intraepidermal nerve fibre density in the acute stage compared with healthy controls based on our previous cohort of patients with chronic WAD2.^53^

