### Statistical analysis

Data will be exported to Stata (V.17, StataCorp, Texas, USA) for analysis. The distribution of the data will be checked for normality, and parametric, or non-parametric methods will be used as appropriate. Participants’ characteristics will be described at all time points.

For objective 1, regression analysis, or non-parametric tests, will be used as appropriate to identify differences in MRI parameters (T2-weighted STIR 4 nerve roots per side, nerve morphology and DTI parameters) and clinical tests (eg, neuropathic pain scores, tests of nerve mechanosensitivity, QST and serum inflammatory markers) between participants with acute WAD2 and age/gender-matched controls. Regression analysis will be used to assess associations with age and height.

For objective 2, recovery of participants with WAD2 will be determined at 6 months with the Neck Disability Index and a global recovery question. The analysis will be conducted with three models using different predictors measured in the acute stage: (a) MRI parameters of neuroinflammation, (b) clinical parameters that reflect neuroinflammation and (c) the addition of MRI to clinical parameters to determine whether this improves predictive strength. The dependence between MRI and clinical assessments will be investigated and composite measures added to the model. In addition, a linear regression will be performed of Neck Disability Index scores on measures of neuroinflammation.

For objective 3, mixed effects modelling will be used to compare MRI and clinical measures between recovered and non-recovered participants with WAD2 over time.

For objective 4, multivariable regression will be used to investigate the relationship of each MRI variable with the clinical parameters of neuroinflammation. In addition, a regression analysis will be performed between clinical measures of neuroinflammation and MRI parameters.

For the substudy, independent t-tests or non-parametric alternatives will be used to compare dermal and intraepidermal nerve fibre density in skin biopsies in patients in the acute phase after whiplash injury with healthy controls. Separate regression models will be used to investigate whether changes in nerve fibre density in the acute stage predict pain persistence at 6 months.

Data reduction techniques (eg, principal components analysis) may be used prior to regression modelling.

Missing data will be managed with multiple imputation strategies.

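### Baseline may fall anywhere in the first 4 weeks after injury and the models described have no term for days since injury; adding one is a cheap safeguard for objectives 2, 3 and 4.

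*Protocol article*

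**What the plan says.** The Objectives section of the protocol article places the MRI comparison "in a cross-section of patients within 4 weeks of injury and healthy controls". Participant recruitment says that patients "will be recruited within 4 weeks of injury". Study design words the window slightly differently: "A total of 115 participants will be recruited following a whiplash injury within 1 month of their original injury". Patients come directly from clinicians, from weekly database searches and through posters. Telephone screening, a posted information sheet and a booked appointment follow, so the delay to baseline will differ between people.

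The outcome is tied to the injury, not to baseline: under Follow-up, participants complete the questionnaires and "answer a self-rated global recovery question 6 months after their injury".

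In the Statistical analysis section, objective 2 is described as follows: "The analysis will be conducted with three models using different predictors measured in the acute stage". The predictors are MRI parameters, clinical parameters, and both together. For objective 4, "multivariable regression will be used to investigate the relationship of each MRI variable with the clinical parameters of neuroinflammation". Age and height appear only under objective 1: "Regression analysis will be used to assess associations with age and height". The section on standardisation adds an adjustment for site. Days since injury is in none of these models. Table 1 and the Clinical assessment section do not list it as a recorded variable, although the injury date must be known to apply the entry window and to time the 6-month contact.

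**The concern.** The study expects its measures to move with time, since objective 3 follows MRI and clinical tests from the acute to the chronic stage. The models nevertheless treat a value from the first days and a value from week 4 as the same acute-stage measurement.

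- **Objective 4** relates MRI to clinical tests. If both settle as days pass, they correlate through timing even where the test says nothing about nerve signal on a given day. The objective seeks low-cost markers, so an association that is partly a shared time trend could be read as more than it is.
- **Objective 2** relates acute MRI to recovery. Unmodelled timing adds noise to the predictor and dilutes its association. If the people assessed later also differ in prognosis, the association is biased as well.
- **Objective 3** compares baseline with 6 months. Baseline floats and follow-up is tied to injury, so the interval varies by up to 4 weeks.

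**Working it through.** **Plan's own figure.** Inputs from Sample size calculation: SD 0.1, ICC 0.45, eight assessments per participant, difference 0.06, 3:1 ratio, 80% power, 5% significance (two-sided assumed).

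Participant-mean SD = 0.1 × sqrt((1 + 7 × 0.45)/8) = 0.1 × sqrt(0.51875) = 0.0720.

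This gives 16 controls and 48 whiplash participants, as stated (power 0.82). The figure does not depend on days since injury.

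**Objective 4.** The documents give no correlation of any measure with days since injury, so the following are assumptions: an excess signal of 0.06 × 2^(−t/h) at day t, half-life h of 7, 14 or 28 days, scan days uniform over 0–28 or 3–28, and a clinical test that correlates 0.3 to 0.5 with days and is otherwise unrelated to MRI.

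- r(MRI, days) = corr(f, t) × SD(f) / sqrt(0.0720² + SD(f)²), where f is the decaying excess.
- Induced correlation ρ = r(MRI, days) × r(test, days).
- Chance of p<0.05 at n = 90 is Φ(z − 1.96) + Φ(−z − 1.96), with z = atanh(ρ) × sqrt(87).

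Upper end (days 0–28, h = 7): SD(f) = 0.0153 and corr(f, t) = −0.944, so the size of r is about 0.20. With a test correlation of 0.5, ρ = 0.098, z = 0.92, and the chance is 0.149 + 0.002 = 15%.

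Lower end (days 3–28, h = 28): SD(f) = 0.0074 and the size of r is 0.10. With a test correlation of 0.3, ρ = 0.031, z = 0.285, and the chance is 0.047 + 0.012 = 6%.

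| Scan days | Size of r(MRI, days), h = 7 to 28 | Chance of p<0.05, test correlation 0.3 to 0.5 |
|---|---|---|
| 3–28 | 0.10 to 0.15 | 6% to 11% |
| 0–28 | 0.12 to 0.20 | 6% to 15% |

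If instead both measures are simply assumed to correlate equally with days at 0.1, 0.2, 0.3, 0.4 or 0.5, the chance is 5%, 7%, 13%, 33% or 66%. The last three need an MRI correlation above anything the decay model gives.

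**Objective 2, timing unrelated to prognosis.** In a logistic simulation (N = 96, 400 runs per scenario) with MRI–days correlations of 0.3 to 0.5, the rejection rate under no true effect was 3.5% to 3.8%, so there was no false association. There was dilution: odds ratio 1.75 to 1.68 unadjusted against 1.88 to 1.99 adjusted. The log odds ratio shrinks by roughly the factor 1 − r². At the 0.10 to 0.20 implied above, that is 0.99 to 0.96, a loss of 1% to 4%.

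**Objective 2, timing related to prognosis.** Take 115 × 0.85 ≈ 98 patients, 49 per recovery group, and assume that non-recovered patients are scanned on day 17 and recovered patients on day 11 on average. The standard error is 0.0720 × sqrt(2/49) = 0.0146.

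- h = 7: difference 0.06 × (2^(−11/7) − 2^(−17/7)) = 0.0090, z = 0.62.
- h = 28: difference 0.06 × (2^(−11/28) − 2^(−17/28)) = 0.0063, z = 0.43.

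Two-sided type I error is 7% to 10%, but it is lopsided: 6.3% to 9.0% finds non-recovered patients lower and 0.5% to 0.8% finds them higher. Under the stronger assumed links in the simulation (MRI–days correlation 0.3 to 0.5, log odds ratio 0.3 to 0.5 per SD of days), null rejection was about 8% to 19% unadjusted and 4% to 6% adjusted, again with odds ratios below 1.

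**Cost of the extra term.** With 48 non-recovered, events per variable go from 48/5 = 9.6 to 48/6 = 8.0, or from 48/10 = 4.8 to 48/11 = 4.4. For objective 4, the plan's rule of 10 participants per variable goes from 90 to 100. The 115 recruited at baseline cover this; the 96 of the objective 1 calculation would not.

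**The case against.** The article condenses a fuller protocol, and covariate lists are commonly left to that document or to the SAP. No covariates are named for objectives 2 to 4 apart from the site adjustment, so the silence is not particular to days since injury, and nothing excludes such a term. This stands, and it is why the point is an improvement and not an error.

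A reader might infer that the natural course of acute injury does confound objectives 2 and 4, with false-positive rates of 32% to 66% in objective 4. The documents do not support that. They expect change from the acute to the chronic stage but show no trend within the first 4 weeks. Rates that high need MRI–days correlations of 0.4 to 0.5, while the plan's effect and SD with the half-lives above give 0.10 to 0.20.

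A reader might also infer that objective 2 would falsely show neuroinflammation predicting poor recovery. In the scenario worked here the bias runs the other way: patients scanned later have lower signal, so that false claim becomes less likely than the nominal 2.5%. The outcome is fixed at 6 months from injury, so timing of baseline does not shift its horizon.

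Finally, objective 4 asks whether clinical tests can serve as markers. If test and signal fall together as inflammation resolves, that is real marker information, and forced adjustment would remove part of it. This stands too, so the adjusted estimate should accompany the unadjusted one, not replace it.

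What remains is that the window is wide, the injury date must already be known, and the described models make no use of it.

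**Conclusion.** The point holds as a low-cost improvement. Baseline timing can vary by up to 4 weeks and no model described accounts for it.

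- **Objective 4:** the chance of a significant association with no link at a given day is about 6% to 15% instead of 5%. This rests on assumed half-lives, an assumed spread of scan days and an assumed clinical-test correlation with days.
- **Objective 2:** there is mild dilution if timing is unrelated to prognosis. There is bias only if the two are related. The documents do not say whether they are, or in which direction.
- **Objective 3:** the interval varies by up to 4 weeks, and no size can be attached to the effect.

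That timing actually confounds any objective is not shown.

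**What to change.** - Record days from injury to the baseline assessment as a study variable.
- Include it as a covariate in the objective 2 models and in the substudy model that predicts persistent pain from nerve fibre density.
- In objective 3, use actual days since injury as the time variable in the mixed model.
- In objective 4, report each MRI–clinical association both unadjusted and adjusted for days since injury, and say that the two answer different questions.
- Align the 4-week and 1-month wordings of the entry window.

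This takes a few sentences of analysis text and uses a date that is already needed. The downside is one parameter per model, which counts against the 5 to 10 predictors allowed for objective 2. No stated sample size has to change, provided that objective 4 uses the full baseline cohort.

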### Baseline and follow-up appointment

Written informed consent will be obtained by a member of the study team at the baseline appointment. Additionally, consent will be gained for use of data/samples in ancillary studies. The following procedures will be carried out (see table 1 for full details):

#### Questionnaires

Patients will complete the following validated questionnaires: Neck Disability Index (NDI),^31 32^ pain detect questionnaire (painDETECT),^33^ short post-traumatic stress inventory (PTSD-8),^34^ Pain Catastrophising Scale (PCS),^35^ Depression, Anxiety and Stress Scale (DASS42),^36^ the quality of life questionnaire (EQ-5D-5L),^37^ and the Impact of Events Scale (IES-Revised).^38^

#### Clinical assessment

Demographic information and type of neck injury sustained will be obtained (ie, speed of impact, direction of collision and initial symptoms). A body chart and Visual Analogue Scale (0–100 mm) will be completed to describe distribution and severity of current symptoms. Current medication intake will also be recorded. Active range of motion of the cervical spine and upper limbs will be assessed and any pain or restriction in range noted (see table 1 for details). A neurological assessment of the upper extremities will be undertaken of cutaneous hypersensitivity and hypoaesthesia using neurotips and cotton wool, and coins will be used to assess thermal sensitivity. Isometric muscle strength and tendon reflexes will also be assessed (table 1).

